### Safety outcomes

Safety outcomes include adverse event evaluation, clinical laboratory indicators (routine blood: hemoglobin, red blood cells, white blood cells, platelets; routine urine: urine protein, urine white blood cells, urine red blood cells; serum biochemistry: urea nitrogen, creatinine, ghrelin, ghrelin, fasting glucose, glycated hemoglobin, potassium, sodium, chloride) and 12-lead electrocardiogram.

### Adverse events

Adverse events will be monitored continuously during treatment and follow-up. Adverse events occur during the course of the study, especially those related to the trial drug, will be followed until the patient’s condition returns to baseline status or stabilizes. If the patient’s condition does not return to baseline or stabilize after follow-up, a note should be documented in the CRF. Any serious adverse events during the clinical trial will be reported to clinical trial supervisor, principal investigator, and drug manufacturer within 24 h. Moreover, the investigator will fill out a serious adverse reaction form to record the time of occurrence, severity, duration, measures taken and regression of the serious adverse event. The investigator will also make a judgment on whether the abnormal laboratory results are clinically significant and provide possible explanations. Abnormal laboratory results resulting from an adverse event that has already been reported should also be recorded as an adverse event. Clinically significant abnormal laboratory tests that meet one or more of the following conditions should be recorded as a separate diagnosis on the adverse events page of the CRF (excluding abnormal laboratory results resulting from an adverse event that has already been reported): 1) if accompanied by clinical symptoms; 2) if a change in the study medication has occurred; or 3) if a change in the combination medication and/or other therapeutic measures is required.

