### Interventions

Eligible participants will be randomly assigned to either the XBP group or the placebo group. If XBP was used prior to randomization, a 2-week drug washout period was implemented to avoid any potential complications of XBP. All participants will receive conventional basic treatment.

Patients in the experimental group will receive XBP (approval number: Z44021843, 4 pills at 60 mg each, po, three times a day). Patients in the control group will receive XBP placebo (4 pills at 60 mg, po, three times a day). The appearance, taste and weight of the placebo will be the same as those of the XBP test drug. Both XBP and placebo will be manufactured by Guangdong Xinbao Pharmaceutical Technology Co., Ltd. And all drugs should meet the requirements of the Chinese National Drug Manufacturing Code. The total treatment course will be 12 weeks.

Conventional basic treatment was provided in accordance with the 2018 Chinese Heart Failure Diagnosis and Treatment Guidelines published by the Chinese Society of Cardiovascular Diseases (Group et al., 2018), including use of ACEIs, ARBs, ARNIs, diuretics, β-blockers and other drugs to reduce cardiac load and enhance myocardial contractility. Each patient should continue to receive the same type and dose of drugs in the conventional basic treatment protocol as that of before enrollment during the treatment period of the trial. No further adjustments can be made during the entire treatment period. If the condition requires a medication adjustment, it should be recorded in the case report form, and investigators should record the combined endpoints and adverse events that occur in patients who receive an increased or decreased dose of medication or type of a different medication.

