### Statistical analysis methods

All statistical tests will be performed using a two-sided test, and a *p* value less than or equal to 0.05 will be considered statistically significant for the difference tested. Dichotomous indicators will be used to describe the number of cases and percentages of each category. Quantitative indicators conforming to normal distribution will be expressed as the “mean ± standard deviation” and skewed data will be described as the median, lower quartile (Q1), and upper quartile (Q3). Comparisons between the two general groups will be analyzed using appropriate methods depending on the type of indicator. Paired *t* test or Wilcoxon rank sum test will be used for comparison between groups for quantitative data, chi-square test or Fisher exact probability method for categorical data, and Wilcoxon rank sum test or CMH test for rank data. The specific applicable statistical methods for each outcome indicator are shown in Table 3.

**TABLE 3 T3:** Outcomes and methods of analyses.

Outcome/variable	Hypothesis	Measures	Methods of analyses
Baseline balance test		Quantitative outcomes (age, temperature, heart rate, respiratory rate, and blood pressure)	*t*-test/Wilcoxon rank-sum test
		Qualitative outcomes (sex, marriage, and previous treatment)	Chi-squared test/Fisher’s exact test/rank-sum test
Primary outcome			
Percent and cases of NT-proBNP decreased ≥30%	decrease occurred		Chi-square test/Fisher’s exact test
Secondary outcome			
NYHA class	decrease occurred		Wilcoxon rank-sum test
6MWT	increase occurred		*t*-test/Wilcoxon rank-sum test
MLHFQ score	decrease occurred	Questionnaire	*t*-test/Wilcoxon rank-sum test
Clinical-endpoint events	decrease occurred	Clinical-endpoint event rate	Log-rank test
NT-proBNP	decrease occurred		*t*-test/Wilcoxon rank-sum test
Echocardiographic parameters	Improvement occurred	LVEF, LVEDD, LVESD	*t*-test/Wilcoxon rank-sum test
TCM symptom scores	decrease occurred	Disappearing rate of main symptoms	Chi-square test/Fisher’s exact test
Safety outcomes			
AEs, SAE		Percent and cases of AEs and SAEs	Chi-square test/Fisher’s exact test

NYHA, New York heart association; 6MWT, 6-min walk distance; MLHFQ, Minnesota living with heart failure questionnaire; LVEF, left ventricular ejection fraction; LVEDD, left ventricular end-diastolic diameter; LVESD, left ventricular end-systolic diameter; AE, adverse event; SAE, serious adverse events; TCM, traditional Chinese medicine.

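### The Adverse events section gives opposite instructions for laboratory abnormalities caused by an already reported adverse event, so event and term counts are not well defined

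*Protocol article*

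**What the plan says.** The Adverse events section deals with laboratory abnormalities in three consecutive steps.

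- Clinical significance is left to the investigator: "The investigator will also make a judgment on whether the abnormal laboratory results are clinically significant and provide possible explanations".
- Results that stem from a known event are then addressed: "Abnormal laboratory results resulting from an adverse event that has already been reported should also be recorded as an adverse event".
- The following sentence defines separate entries in the case report form: "Clinically significant abnormal laboratory tests that meet one or more of the following conditions should be recorded as a separate diagnosis on the adverse events". It carries a parenthesis, "excluding abnormal laboratory results resulting from an adverse event that has already been reported", and lists three alternative conditions, which begin "1) if accompanied by clinical symptoms; 2) if a change in the study medication has occurred; or 3) if a change in the combination medication".

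Under Data collection and management, adverse events are to be coded with MedDRA 21.0 or later. Table 3, under Statistical analysis methods, gives the safety measure as "Percent and cases of AEs and SAEs", compared by chi-square or Fisher's exact test. Recruitment names six centres.

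**The concern.** A rule on what goes onto the adverse event page acts at the site, before any analysis. If it can be read in two ways, the data differ by reader, and an analysis plan written later cannot reliably recover which reading a given entry followed.

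Here the same finding, for example a raised creatinine that follows a reported event, is a further adverse event under one sentence and is barred from separate entry under the next. Any tabulation of the number of events, or of how often a laboratory term occurs, would then partly reflect which sentence a centre followed. Safety is part of the trial's stated aim, so these tables will be read.

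**Working it through.** The article gives no adverse event rates and no figure to reproduce. The check is first one of wording, then a count under assumed rates.

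**Step 1. Apply the two sentences to each kind of laboratory abnormality.**

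| Abnormality | First sentence | Next sentence |
|---|---|---|
| Caused by a reported event; clinically significant; meets at least one condition | Record as an adverse event | Excluded from separate entry |
| Caused by a reported event; not clinically significant, or meets no condition | Record as an adverse event | No separate entry called for |
| Not caused by a reported event; clinically significant; meets at least one condition | Silent | Separate entry |
| Not caused by a reported event; clinically significant; meets no condition | Silent | Separate entry not required |

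The first row is a direct conflict. The second row is also odd: read literally, a minor abnormality would be recorded when it is secondary to something else, while a similar one standing alone would not have to be. The third and fourth rows hold no conflict.

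**Step 2. Which measures change?**

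Inputs: 142 patients per arm (Sample size section). Assumed: 30% of patients have one adverse event each, and a fraction f of those events brings one secondary laboratory abnormality.

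- Patients with an event: 0.30 × 142 = 42.6, taken as 43.
- Events if secondary results are excluded: 43.
- Events if secondary results are also recorded: 43 + f × 43.

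| f | Extra entries | Events, excluded | Events, also recorded | Patients with any event, either reading |
|---|---|---|---|---|
| 10% | 4.3, taken as 4 | 43 | 47 | 43/142 |
| 30% | 12.9, taken as 13 | 43 | 56 | 43/142 |
| 50% | 21.5, taken as 22 | 43 | 65 | 43/142 |

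The last column is constant by construction: a secondary abnormality occurs only in a patient already counted. The event count moves by 4/43 = 9% to 22/43 = 51% under these assumptions. Counts by MedDRA term move too, since each extra entry is coded in its own right.

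**Step 3. Does this reach Table 3?**

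It depends on what is meant by cases. The Sample size section uses the word for patients, and a chi-square or Fisher test fits a comparison of patients. On that reading the any-event comparison in Table 3 is unaffected. If the word is taken to mean events, the count is affected as above. The table does not say which.

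**The case against.** **A harmonising reading exists.** The first sentence could mean that the result is noted under the existing event, and the second that it is not a separate diagnosis. Or the first sentence may have lost a negative. Either is plausible, but the text says neither, and recording something as an adverse event, read plainly, conflicts with the exclusion.

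**The main comparison is safe.** This stands. The percentage of patients with any adverse event is the same under both readings. Staff apply the rule without knowing the arm (Blinding section), so the inconsistency adds noise to event counts, with no demonstrated tilt.

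A reader might also infer three stronger points, which the article does not support:

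- *That clinically significant but symptom-free abnormalities are dropped.* The three conditions are alternatives. A silent abnormality still gets its own entry if the study drug was changed, or "if a change in the combination medication and/or other therapeutic measures is required". Only abnormalities with neither symptoms nor action fall outside. A threshold based on symptoms or action is a design choice, not an error.
- *That the ban on changing background treatment widens this gap.* Interventions does say "No further adjustments can be made during the entire treatment period", but goes straight on to provide for adjustments that the patient's condition requires, to be recorded in the case report form.
- *That laboratory and ECG findings escape analysis because Table 3 has no row for them.* Safety outcomes lists both as outcomes in their own right, Table 2 schedules them at every visit, and the text above Table 3 gives general methods by type of data. A dedicated row is detail commonly left to the analysis plan.

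Nor can it be said that the comparison does double-count. That happens only where a site follows the first sentence, and only in counts of events or terms.

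**Conclusion.** The contradiction is real and confined to one kind of finding: laboratory abnormalities secondary to an adverse event already reported. It leaves the number of events and the MedDRA term counts undefined for those findings, and centres may differ. The illustrated size, 43 events against 47 to 65 per arm, rests wholly on an assumed 30% event rate and an assumed 10% to 50% share with a secondary laboratory change. The true size cannot be obtained from the article. The proportion of patients with any adverse event does not move, and no bias for or against either arm is shown. This is a clarification worth making because it governs data being collected now. It does not undermine the safety comparison.

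**What to change.** - Reconcile the two sentences into one rule for all six centres: a laboratory abnormality caused by an already reported adverse event is recorded once, under that event, and not as a further event. Delete the first sentence or correct it to say this. Leave the three conditions for separate entries as they are.
- State in Table 3 that its percentages and cases count patients with at least one event.
- Put the same rule in the instructions for completing the case report form, and check adverse event entries already made against it, since the article reports that recruitment is under way.

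The cost is small: a wording change (which the Quality control section says needs ethics committee approval before use), a note to sites, and a one-off check of existing entries. No new tests, visits or patients are needed.

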### Data collection and management

Study data will be recorded on the paper CRF or electronically *via* the eCRF. The paper CRFs will be sent to the clinical center and Shunde Hospital of Guangzhou University of Chinese Medicine will provide training and support to the investigators by using the eCRF system. To promote participant retention and completion of follow-up visits, frontline investigators will inform patients the time of follow-up visit to hospital by phone and WeChat. This work will be performed by two independent investigators.

The data management process needs to comply with regulatory requirements such as “Quality Management Standards for Drug Clinical Trials” (Zhang et al., 2021) and “Technical Guidelines for Clinical Trial Data Management Work” (Wang et al., 2013)to ensure the traceability of clinical trial data. The data manager will design the database based on the CRF using Epidata software and will release it after testing. The clinical research coordinator (CRC) is responsible for entering the data on the CRF into the database, and the data entry is performed in a secondary manner. The data manager will prepare the data verification SAS program based on the data verification plan and then generate a data query form, which is returned to the data manager by the clinical reviewer after the investigator has answered the queries, and the data manager will revise the database accordingly. MedDRA 21.0 or later will be used for adverse event coding. After database cleanup is completed, the data manager will write the data verification report for use in data verification meetings. The database lock list is completed at regular intervals and the database lock is completed according to the database lock procedure. After the database lock is completed, the data manager will export the data file in SAS format and send it to the statistician for statistical analysis. The personal information about of the potential and enrolled participants is confidential and will be protected throughout the trial, and researchers will be expected to maintain data confidentiality for 5 years after trial termination.

## Statistical analyses

### Statistical analysis data sets

Subjects in the trial will be divided into full analysis set (FAS), per-protocol analysis (PPS), and a safety analysis set (SAS). Efficacy analysis will be performed on the FAS and PPS. All baseline demographics will be analyzed on the FAS, and safety evaluation will be performed on the SAS.

### Statistical analysis methods

All statistical tests will be performed using a two-sided test, and a *p* value less than or equal to 0.05 will be considered statistically significant for the difference tested. Dichotomous indicators will be used to describe the number of cases and percentages of each category. Quantitative indicators conforming to normal distribution will be expressed as the “mean ± standard deviation” and skewed data will be described as the median, lower quartile (Q1), and upper quartile (Q3). Comparisons between the two general groups will be analyzed using appropriate methods depending on the type of indicator. Paired *t* test or Wilcoxon rank sum test will be used for comparison between groups for quantitative data, chi-square test or Fisher exact probability method for categorical data, and Wilcoxon rank sum test or CMH test for rank data. The specific applicable statistical methods for each outcome indicator are shown in Table 3.

**TABLE 3 T3:** Outcomes and methods of analyses.

Outcome/variable	Hypothesis	Measures	Methods of analyses
Baseline balance test		Quantitative outcomes (age, temperature, heart rate, respiratory rate, and blood pressure)	*t*-test/Wilcoxon rank-sum test
		Qualitative outcomes (sex, marriage, and previous treatment)	Chi-squared test/Fisher’s exact test/rank-sum test
Primary outcome			
Percent and cases of NT-proBNP decreased ≥30%	decrease occurred		Chi-square test/Fisher’s exact test
Secondary outcome			
NYHA class	decrease occurred		Wilcoxon rank-sum test
6MWT	increase occurred		*t*-test/Wilcoxon rank-sum test
MLHFQ score	decrease occurred	Questionnaire	*t*-test/Wilcoxon rank-sum test
Clinical-endpoint events	decrease occurred	Clinical-endpoint event rate	Log-rank test
NT-proBNP	decrease occurred		*t*-test/Wilcoxon rank-sum test
Echocardiographic parameters	Improvement occurred	LVEF, LVEDD, LVESD	*t*-test/Wilcoxon rank-sum test
TCM symptom scores	decrease occurred	Disappearing rate of main symptoms	Chi-square test/Fisher’s exact test
Safety outcomes			
AEs, SAE		Percent and cases of AEs and SAEs	Chi-square test/Fisher’s exact test

NYHA, New York heart association; 6MWT, 6-min walk distance; MLHFQ, Minnesota living with heart failure questionnaire; LVEF, left ventricular ejection fraction; LVEDD, left ventricular end-diastolic diameter; LVESD, left ventricular end-systolic diameter; AE, adverse event; SAE, serious adverse events; TCM, traditional Chinese medicine.

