*Bufonis Venenum*	Chan Su	蟾酥	Bufo bufo gargarizans Cantor	the dry secretion of Bufo bufo gargarizans Cantor or Bufo melanostictus Schneider
*Cervi Cornu Pantotrichum*	Lu Rong	鹿茸	Cervus nippon	the unossitized, densely hairy young horn of a buck by Cervus Nippon Temminck or Cervus elaphus Linnaeus
Cinnamomum camphora (L.) J. Presl	Bing Pian	冰片	Borneolum Syntheticum	-

The clinical efficacy and safety of XBP in the treatment of CHF is still unclear. Therefore, we conducted a multicenter, randomized, double-blind, placebo-parallel controlled trial to try to elucidate the clinical efficacy and safety of XBP in the treatment of CHF, to provide high-quality evidence-based medical evidence. The main hypothesis of this study is that XBP is superior to placebo in patients with CHF when combined with conventional therapy.

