## Methods and analyses

### Design and settings

This study is a multicenter, stratified, randomized, double-blind, placebo-controlled, parallel-group superiority trial planned to be implemented in patients with CHF with “heart-kidney yang deficiency syndrome.” A total of 284 participants will be recruited. After participants are enrolled and provided written informed consent, they will be randomly assigned, in a 1:1 ratio, to either the XBP group or the placebo group. The trial will consist of a 1-week screening period, 12-week intervention period, and 12-week follow-up period. The study flow is shown in Figure 1.

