### Randomization and allocation

Participants will be randomly assigned, in a 1:1 ratio, to the experimental and control groups using the central randomization system of the Drug Clinical Trial Management Office, Shunde Hospital of Guangzhou University of Chinese Medicine. Randomization groups will be stratified by the central stratification method, generating random numbers, and generating randomized results by SAS statistical software (version 9.4; SAS Institute, Cary, NC, United States). The randomization number and drug number will be separately obtained by each study subcenter investigator using a sequential number in the central randomization system. All center numbers, sequence numbers, randomization numbers, and drug numbers will be managed by the statistical unit.

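### The text names a paired t test for comparing two independent arms on quantitative outcomes; it should name an independent two-sample test

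*Protocol article*

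**What the plan says.** The general rule for quantitative data in the protocol article's Statistical analysis methods section is "Paired *t* test or Wilcoxon rank sum test will be used for comparison between groups for quantitative data". The section then points to a table for detail: "The specific applicable statistical methods for each outcome indicator are shown in Table 3". For 6MWT, MLHFQ score, NT-proBNP and the echocardiographic parameters, Table 3 lists a t test or the Wilcoxon rank-sum test. It does not say whether the t test is paired or independent. The same label stands in the row for quantitative baseline variables such as age and blood pressure.

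The design is described under Design and settings as a "multicenter, stratified, randomized, double-blind, placebo-controlled, parallel-group superiority trial". Under Randomization and allocation, "Participants will be randomly assigned, in a 1:1 ratio, to the experimental and control groups". No section describes matched pairs or a crossover. The main hypothesis in the Introduction is that "XBP is superior to placebo in patients with CHF when combined with conventional therapy".

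**The concern.** A paired t test needs a natural link between each observation in one set and one observation in the other. Two separately randomised arms have no such link. Only the word *paired* in the text says which t test is meant, and it names one that does not suit the design.

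What is at stake is the analysis of every quantitative secondary outcome. A test that cannot be run as written leaves the analyst to choose a replacement after the data exist. If someone runs it anyway, the result depends on how the rows happen to be sorted, and patients without a partner are lost.

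**Working it through.** **Inputs.** Two-sided tests at 0.05 (Statistical analysis methods: "All statistical tests will be performed using a two-sided test, and a *p* value less than or equal to 0.05"). Response rates of 31.98% and 50%, power 80%, 114 per group before and 142 after allowance for 20% missed visits (Sample size section). The effect sizes used in steps 3 and 4 are assumptions; the protocol gives none for the quantitative outcomes.

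**1. The plan's own figure.** For two independent proportions with unpooled variance, n = (1.960 + 0.842)² × [0.3198 × 0.6802 + 0.50 × 0.50] / (0.50 − 0.3198)² = 7.849 × 0.4675 / 0.03247 = 113.01, rounded up to 114. This matches the protocol. Dropout: 114 / 0.80 = 142.5, against 142 stated. The sample size rests on the binary primary outcome, which Table 3 tests by chi-square or Fisher's exact test. The choice of t test does not enter it.

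**2. The two tests side by side, n per arm.** Let c be the sample covariance across whichever pairs were formed.
- Independent: t = (mean₁ − mean₂) / √[(s₁² + s₂²)/n], with 2n − 2 = 226 degrees of freedom at n = 114.
- Paired: t = (mean₁ − mean₂) / √[(s₁² + s₂² − 2c)/n], with n − 1 = 113 degrees of freedom.

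The numerators are the same. The true covariance between unrelated patients is zero, but its sample value c changes with the ordering of rows, and so does the p value. The formula also requires equal n. That is unlikely here, because the plan expects 20% to miss visits and analyses a per-protocol set as well as the full analysis set. As an illustration with assumed arms of 112 and 116, the paired test cannot be computed unless 4 patients are discarded from the larger arm.

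**3. Size of the effect when rows are paired arbitrarily** (20,000 simulated trials, normal data, 114 per arm):

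| | Paired, arbitrary | Independent | Conclusions differ |
|---|---|---|---|
| No difference (type I error) | 5.0% | 5.1% | 0.8% of trials |
| Difference of 0.375 SD (power) | 80.4% | 80.7% | 2.1% of trials |

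In one simulated data set the independent p value was 0.52. Across 5,000 re-pairings of the same data, the paired p value ran from 0.42 to 0.58. Average operating characteristics are nearly unchanged, but the individual result is not reproducible.

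**4. If *paired* were taken to mean before/after within each arm.** The protocol does not plan this; the step shows only what such a misuse would do. There is no treatment effect, and both arms change by the same assumed amount (in SDs of change, 114 per arm):

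| Common change | XBP arm significant | XBP significant, placebo not | Between-arm independent test |
|---|---|---|---|
| 0.1 SD | 19% | 15% | 4.9% |
| 0.2 SD | 56% | 25% | 5.0% |
| 0.3 SD | 89% | 10% | 5.1% |
| 0.5 SD | nearly 100% | <1% | 5.0% |

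The second column is power to detect a change that really occurred in that arm. It is not a type I error. The third column is roughly P(1 − P), where P is the second column. It cannot exceed about 25%, so the 0.2 SD row is close to the worst case.

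**The case against.** The strongest reply is that this is a one-word slip whose intended meaning can be recovered. The sentence itself says the comparison is between groups. Its alternative is the independent-samples rank-sum test. The section defers to Table 3 for specific methods, and Table 3 omits the word *paired*. The baseline row of Table 3 uses the same t-test label for age and blood pressure, where only an independent test is possible. Much of this stands, and it lowers the severity. It does not remove the error: an unqualified t test is less specific than the text and does not retract it. For the same reason, it would be too strong to say that the text and the table contradict each other.

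A reader might infer that the trial plans within-arm before/after tests as its evidence of efficacy, citing Table 3's hypothesis column ("decrease occurred"). The document does not support this. No section plans such a test. The Secondary outcome indicators section speaks of differences between groups for the TCM scores. The same hypothesis label is attached to endpoint events (log-rank), the primary responder proportion (chi-square or Fisher) and NYHA class (rank-sum), all of which are between-arm tests. The column gives loose direction labels.

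A reader might also set the 56% in step 4 against a nominal 5%. That comparison is wrong, because the within-arm null hypothesis is false in that simulation.

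**Conclusion.** The rule is wrong as written. It assigns a paired t test to two independent arms, is inconsistent with the rank-sum test in the same sentence, and is not corrected by Table 3. The practical defects are that the test is undefined with unequal arms, depends on row order, and drops unmatched patients. There is no material inflation of type I error.

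The scope is 6MWT, MLHFQ score, NT-proBNP level, LVEF, LVEDD, LVESD and quantitative baseline comparisons. The primary outcome, the sample size, NYHA class, endpoint events and adverse events are untouched. Within-arm testing remains a possible misuse only. If it were adopted, a spurious contrast between the arms would appear in about 15%, 25%, 10% or under 1% of trials, for an assumed common change of 0.1, 0.2, 0.3 or 0.5 SD. The simulation figures assume normal data and equal arms of 114. This should be fixed, but it does not threaten the primary conclusion.

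**What to change.** In Statistical analysis methods, replace the paired t test with an independent two-sample t test. Make the same specification in Table 3, so that each quantitative outcome is tested as XBP versus placebo. Add one sentence stating that any paired or signed-rank test within an arm is descriptive and will not be used to claim efficacy. Wording the Table 3 hypotheses as differences between the arms would remove the remaining looseness.

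The change amounts to a few words in the text and the table. It needs no more patients, visits or data, and it leaves the sample size as it is. The trial is recruiting, so the change should go through the ethics approval that the Quality control section requires for protocol modifications, and be in place before unblinding.

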### Sample size

Investigators conducting the trial estimate the sample size based on the level of NT-proBNP, the main efficacy indicator. The literature (Li et al., 2013), showed that NT-proBNP levels decreased by more than 30% after 12 weeks of conventional basic treatment combined with placebo in 31.98% of patients, and NT-proBNP levels decreased by more than 30% after 12 weeks of conventional basic treatment combined with herbal medicine in 47.95% of patients. Therefore, it is expected that the percentage of patients with NT-proBNP levels decreasing more than 30% after 12 weeks of conventional basic treatment combined with XBP will be 50%. Thus, assuming *α* = 0.05 and *β* = 0.20, the calculated sample size required for each group was 114 cases after substituting the above values using PASS11 software. Considering that 20% will miss visits, the sample size was adjusted to 142 cases in each group. The total number of cases required for both groups was 284.

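### Randomisation is described as stratified, but Table 3 fixes an unstratified chi-square or Fisher test for the primary outcome: valid and at about the planned power, yet conservative when strata differ

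*Protocol article*

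**What the plan says.** Under Design and settings the study is a "multicenter, stratified, randomized, double-blind, placebo-controlled, parallel-group superiority trial". Under Randomization and allocation, "Randomization groups will be stratified by the central stratification method". No stratification factor is named. Six centres are listed under Recruitment, and the statistical unit holds the centre numbers, so centre is the natural reading.

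Statistical analysis methods assigns the "chi-square test or Fisher exact probability method for categorical data" and refers to Table 3 for the method that applies to each outcome. In Table 3 the primary row, which begins "Percent and cases of NT-proBNP decreased ≥30", carries a chi-square or Fisher's exact test and nothing else. The CMH test is mentioned only for rank data. No outcome has a stratum, centre term or baseline covariate attached to it.

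The Sample size section compares two proportions: "conventional basic treatment combined with placebo in 31.98% of patients" against an expectation that the percentage under "conventional basic treatment combined with XBP will be 50", "assuming *α* = 0.05 and *β* = 0.20". It arrives at 114 per group, raised to 142 for 20% missed visits, 284 in total.

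**The concern.** Stratified allocation balances the strata across the arms. Differences in responder rate between strata therefore no longer add to the variability of the treatment difference. A plain chi-square test computes its variance as if allocation had been simple and so still counts that variation. Its standard error is then too large, the test rejects too rarely when there is no effect, and a small efficiency gain already built into the design goes unused.

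This concerns the one confirmatory test of the trial. The article does not leave the matter open: it states the primary test, and states it without the strata. It also offers two tests for that outcome with no rule for choosing between them.

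**Working it through.** **1. The plan's own figure.** Inputs from Sample size: p0 = 0.3198, p1 = 0.50, α = 0.05, power 0.80. Statistical analysis methods adds that "All statistical tests will be performed using a two-sided test". With unpooled variance,

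n = (1.960 + 0.842)² × [p0(1 − p0) + p1(1 − p1)] / (p1 − p0)²
= 7.849 × (0.2175 + 0.2500) / 0.1802² = 113.007, rounded up to 114.

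This matches the stated figure. The pooled formula gives 116, and by that formula the power at 114 per arm is 79.4%. For dropout, 114 / 0.8 = 142.5, stated as 142. The sample size is that of an unstratified, unadjusted comparison of two proportions, so sample size and test agree with each other.

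**2. Why the plain test is conservative.** Write p for the overall responder rate and p_k for the rate in stratum k. With balanced allocation within strata, the true variance of the difference is proportional to the average of p_k(1 − p_k), which equals p(1 − p) minus the between-stratum variance of p_k. The chi-square test uses p(1 − p). With r the ratio of the first to the second, type I error is about 2[1 − Φ(1.96/√r)]. For example, r = 0.92 gives 1.96/√0.92 = 2.043 and a type I error of about 4.1%. With identical strata r = 1 and nothing is lost.

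**3. Size under assumed centre variation.** Simulation with six unequal centres, allocation balanced within centre, 114 evaluable per arm, 31.98% against 50%. The centre standard deviation (SD, logit scale) is an assumption, because the article gives no figure.

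| Centre SD | Type I error, chi-square | Power, chi-square | Power, CMH | Power forgone (points) |
|---|---|---|---|---|
| 0 | 5.0% | 79.8% | 79.9% | 0.1 |
| 0.3 | 4.8% | 79.9% | 80.1% | 0.2 |
| 0.5 | 4.7% | 80.3% | 81.1% | 0.8 |
| 0.8 | 4.1% | 81.3% | 83.8% | 2.5 |
| 1.2 | 3.3% | 82.1% | 87.3% | 5.2 |

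Type I error of the CMH test stays at about 5% throughout. For scale, SD 0.8 means control responder rates of about 16% to 49% at one SD either side, and SD 1.2 means about 10% to 56%. These are large differences between centres.

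**4. Chi-square or Fisher.** This needs no assumption about centres. Exact power at 114 per arm, 31.98% against 50%, is 79.7% for chi-square and 75.7% for Fisher. With 31.98% in both arms, Fisher's type I error is 3.7%. The expected counts per arm are 114 × (0.3198 + 0.50)/2 = 46.7 responders and 114 − 46.7 = 67.3 non-responders, so small counts give no reason to use Fisher.

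**5. Baseline as covariate.** A separate simulation with six equal centres also gave the baseline value an assumed prognostic strength (0 to 1.0 log-odds per SD) and used centre SDs of 0 to 1.0. A logistic model with centre and baseline had 79% to 89% power, up to about 9 points above the plain test. The upper end rests wholly on those assumptions.

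**The case against.** The strongest reply is that nothing is broken. The trial was sized for an unadjusted comparison, that comparison is what Table 3 specifies, and its power stays at about 80% in every scenario above. The error is in the safe direction: a positive result would not be made less reliable. Up to a centre SD of 0.5 the gain is under 1 point. The setting also gives little reason to expect extreme variation: the outcome is a within-patient percentage change in a laboratory marker, two of the six sites are branches of one hospital, and the Discussion describes a population mainly from southern China. All of this stands, and it keeps the point modest.

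Several stronger readings are tempting and should be resisted:

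- A reader might infer that power falls short of plan. It does not; what is forgone lies above the planned level.
- A reader might infer that ignoring the strata inflates false positives. The effect runs the other way.
- A reader might say that baseline NT-proBNP is thrown away. It is the denominator of the 30% decrease and so is part of the outcome; it is only not used as a covariate.
- A reader might take stratification by centre as stated. It is the likely meaning, but no factor is named.
- A reader might count the Fisher figure as an expected loss. It matters only if Fisher is chosen, which the usual small-count convention would not lead to here.

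The reply that the matter belongs to the unseen analysis plan does not stand. Supportive models can be left to it, but the article itself fixes the primary test, and an analysis plan that named a stratified test would contradict Table 3.

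**Conclusion.** The mismatch holds: randomisation is described as stratified, and the primary test takes no account of the strata, whichever factor was used. The consequence is a valid but conservative test, with type I error of about 4.7%, 4.1% and 3.3% at centre SDs of 0.5, 0.8 and 1.2, and 0 to about 5 power points forgone, under 1 point up to SD 0.5. These figures rest on an assumed range of centre variation, on centre being the factor, and on allocation balanced within centres. If centres hardly differ, the two tests give practically the same answer. This is an improvement worth making because it needs no extra patients; it is not a threat to the trial's conclusions.

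**What to change.** Make these changes before unblinding:

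- Name the stratification factor or factors under Randomization and allocation.
- In Table 3, make the primary test a Cochran-Mantel-Haenszel test stratified by those factors (centre, if that is the factor), and report the stratified risk difference with its 95% CI.
- Keep the plain chi-square test as a sensitivity analysis.
- Remove Fisher's exact test from the primary row.
- Optionally, add a logistic model with the stratification factors and log baseline NT-proBNP, labelled as supportive only.

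The cost is wording in Table 3 and the analysis plan, submitted as a protocol modification for ethics approval as the Quality control section requires. The sample size, visits and data collection do not change.
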